### Statistical analysis

2.5

Health examination outcomes and individual dose monitoring data will be collected from Chongqing CDC personal dose monitoring system and National Radiation Health Information Platform (35, 40). Data quality will be assessed using the “dataquieR” package in R software, following the framework proposed by Schmidt et al. (52, 53). If radiation dose data is missing, we can use the notional dose to supplement the missing data, which represented the average dose for the same occupation during that year (54). The exposure–lag–response association between radiation dose and health outcomes will be evaluated using a distributed lag non-linear model (DLNM) combined with either a generalized linear model (GLM) or multiple generalized additive models (GAM) (55). For certain outcomes, if necessary, a nested case–control design will be applied, with controls time-matched to cases to ensure a comparable number of total person-time observations. A cross-basis function in the DLNM, utilizing natural spline basis functions, will be employed to construct a two-dimensional matrix that integrates radiation dose and lag time, thereby enabling a detailed analysis of the lag structure (55). For continuous health outcomes, a Gaussian distribution will be used as the link function; for count outcomes, a Poisson distribution will be applied; and for categorical outcomes, a binomial distribution will be employed in the GLM framework. Given the non-linear relationship between radiation dose and health outcomes, GAM will be applied to assess potential dose–response relationships. For non-linear relationships, piecewise linear spline models will classify participants into different exposure categories based on radiation exposure thresholds and will use these categories to assess linear dose–response relationships. Several sensitivity analyses were conducted to assess the robustness of the results. First, GAM or GLM analyses will be rerun after excluding cases with missing data for both controls and cases. Second, to account for potential interaction effects, interaction models were fitted by including variables such as exposure dose levels, age, gender, and occupational category in relation to health outcomes. Third, if significant interaction effects were identified, stratified analyses were performed, such as by occupational category or exposure dose levels, to explore these effects further. All analyses were carried out using R software (version 4.4.1). For normally distributed data, continuous variables are presented as mean ± standard deviation (SD); skewed data are presented as median or interquartile range (IQR). *p* values <0.05 were considered as statistically significant.

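### The piecewise-spline step is described as putting workers into dose categories, and dose level is listed as an interaction and stratifying variable; dose should stay continuous, with preset knots

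*Protocol article*

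**What the plan says.** All the relevant text is in section 2.5, Statistical analysis.

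- The main model is a distributed lag non-linear model whose cross-basis uses natural splines, so dose enters as a continuous variable.
- The additive model of dose-response takes curvature as its starting point; the sentence on it begins "Given the non-linear relationship between radiation dose and health outcomes, GAM will be applied to assess potential".
- The next step applies wherever curvature is present. There, "piecewise linear spline models will classify participants into different exposure categories based on radiation exposure thresholds". Those categories are then used to assess linear dose-response. The section gives no threshold value, number or source.
- Among the sensitivity analyses ("Several sensitivity analyses were conducted to assess the robustness of the results"), the second is that "interaction models were fitted by including variables such as exposure dose levels, age, gender, and occupational category in relation to health outcomes".
- The third is conditional on the second: "if significant interaction effects were identified, stratified analyses were performed, such as by occupational category or exposure dose levels".
- One significance rule covers everything: p "values <0.05 were considered as statistically significant". The section mentions no allowance for choosing a threshold.

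**The concern.** Two things are badly specified.

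**The piecewise step names one method and describes another.** A piecewise linear spline fits connected slopes to continuous dose. Classifying workers and then looking for a linear trend over the classes is a different analysis, with less information and a different error rate. An analyst could defend either from this sentence. If the thresholds also came from the data being tested, p<0.05 would no longer mean 5%.

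**Dose level appears as a variable that modifies or stratifies.** The effect under study is the effect of dose. Crossing dose with its own level is only another expression of curvature, which the spline terms already carry. Stratifying by dose level removes most of the dose range within each stratum. If dose is right-skewed, only the top stratum keeps usable precision. A significant slope there and nowhere else could then be read as an effect confined to high doses, when it reflects only where the precision lies.

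The study concerns low-dose exposure, so an apparent threshold is a result that readers would take seriously.

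**Working it through.** The plan gives no figure for this step, so there is none to reproduce. The checks measure what the wording costs.

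**Inputs from the article**
- Analysed number 660, recruited 825 (Sample size calculation). 825 × 0.80 = 660.
- White cell count SD 1.40 (same section).
- Mean annual dose 0.56 mSv (Baseline information).
- Significance level 0.05 (Statistical analysis).

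**Assumptions not in the article**
- Dose is lognormal with log-SD 0.8, scaled to the stated mean. The article gives no spread, so other values are shown where they matter.
- One independent outcome per worker, no true dose effect, and no preliminary test for curvature.
- For a searched threshold: 33 candidates from the 10th to the 90th percentile of dose.

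**1. Information lost by categorising.** For a linear effect, a category score keeps a fraction r² of the information on the slope, where r is the correlation between dose and score. With tertiles scored 1, 2, 3:
- lognormal, log-SD 0.8: r² ≈ 0.48, equivalent to 660 × 0.48 ≈ 317 workers with continuous dose;
- normal: r² ≈ 0.79, equivalent to 660 × 0.79 ≈ 521 workers.

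**2. False-positive rate with no dose effect** (2,000 or more simulated datasets; Monte Carlo error about 1 percentage point or less)

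| Procedure, nominal 5% | Threshold preset | Threshold searched in same data |
|---|---|---|
| Two-group comparison at the cut | 4–6% | about 35% (33–37% across runs) |
| Change of slope at the knot | 4–6% | about 17% (16–17%) |
| Either segment slope p<0.05 (two tests) | about 9% | 22–24% |

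The last row counts two tests, so about 9% arises without any search. The first two rows isolate the effect of searching.

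**3. Precision within dose strata.** The standard error of a slope is σ / √(n × Var(dose)). In a tertile, n becomes n/3 and Var becomes the within-tertile variance. The ratio to the full-cohort standard error is therefore √(3 / share), where share is the within-tertile variance divided by the total variance.

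Lognormal, log-SD 0.8:
- lowest tertile: √(3 / 0.0146) ≈ 14;
- middle tertile: √(3 / 0.0234) ≈ 11;
- highest tertile: √(3 / 1.392) ≈ 1.5.

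The assumed spread matters. From log-SD 0.5 to 1.0, the lowest-tertile ratio runs from 7.5 to 24 and the highest from 1.8 to 1.3. With normal dose the three ratios are about 3.3, 7 and 3.3.

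**The case against.** **Thresholds chosen from the data.** A reader might infer that the cut-points will be picked from the fitted curve and tested in the same data. The step does follow a finding of non-linearity, and the models are said to do the classifying. The only dose value that the article calls a threshold, 20 mSv a year (Dosimetry data), cannot divide a cohort said to lie below it. Even so, the text describes no search and no breakpoint estimation. Elsewhere the article uses the word for a fixed external limit, and the values may be set in a full protocol or analysis plan that is not shown. This part of the objection stands: the inflated error rates are conditional, and the missing threshold values are not themselves a fault.

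**Dose crossed with dose level.** A reader might also take the plan to fit a dose-by-dose-level interaction. The list, "interaction models were fitted by including variables such as exposure dose levels, age, gender, and occupational category", can equally mean dose level crossed with age, gender or occupation, which is sensible. The text supports both readings. Simply deleting dose level from that list could even remove the exposure from the interaction models.

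**Effect on the main result.** Some may conclude that the main result is biased. It is not: the main lag model keeps dose continuous, the interaction and stratified analyses are sensitivity analyses, and dose stratification is one example under a condition. Restricting the dose range costs precision but does not by itself bias the slope.

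**Loose wording.** The categories may simply mean the spline's segments. If so, rewording is enough, but the sentence then goes on to use categories of participants for the dose-response assessment, which segments would not need.

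**Conclusion.** The point holds in a limited form. The piecewise sentence misdescribes its method. Taken literally it discards information on a linear slope: about half under lognormal dose with log-SD 0.8, and about a fifth under normal dose. If the thresholds are derived from the same data and tested at p<0.05 without allowance, the error rate is roughly 17% to 35%, depending on the test, against about 5% for a preset cut. That conditional result rests on the assumed dose spread, the assumed search range and one outcome per worker. If dose level is used to modify or stratify the dose effect, it adds nothing beyond curvature and gives within-stratum standard errors about 1.5 to 14 times larger. The harm is lost precision and possible misreading in secondary analyses, not bias in the main result. It should still be put right, because it is cheap to do.

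**What to change.** - Rewrite the piecewise sentence so that dose stays continuous, with knots set in advance, for example at dose quantiles.
- Label any breakpoint estimated from the data as exploratory, and give it an interval that allows for its selection, such as a bootstrap interval.
- State the interactions as dose by age, dose by gender and dose by occupational category.
- Do not use dose level as a modifier or stratifier of the dose effect. In the sentence "stratified analyses were performed, such as by occupational category or exposure dose levels", keep occupational category and drop dose level.

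The cost is a change of wording and slightly less analysis. The small downside is that a table by dose category becomes descriptive only.

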
### Baseline information

2.6

The basic characteristics of the study population in 2016 are presented in Table 1.

**Table 1 tab1:** Characteristics and health outcomes of radiation workers in Chongqing, 2016.

	Mean ± SD / M[IQR]/ n (%)
Age	37.00 [31.25, 47.00]
Gender *n* (%)	
Male	30 (60)
Female	20 (40)
Education *n* (%)	
Associate degree or below	7 (14)
Undergraduate	37 (74)
Master’s degree	6 (12)
Marital status *n* (%)	
Unmarried	18 (36)
Married	32 (64)
White blood cells (10^9^/L)	5.72 ± 1.46
Red blood cells (10^12^/L)	4.88 ± 0.65
Hemoglobin (g/L)	142.90 ± 21.40
Platelets (10^9^/L)	214.32 ± 58.01
Hematocrit (%)	42.77 ± 5.63
Mean corpuscular hemoglobin (pg)	30.20 [28.65, 30.98]
Alanine transaminase (U/L)	19.75 [15.90, 29.38]
Blood urea nitrogen (mmol/L)	5.12 ± 1.35
Creatinine (μmol/L)	58.05 [51.95, 72.90]
Uric acid (umol/L)	235.51 ± 51.81
Gamma-glutamyl transferase (U/L)	17.00 [13.00, 26.50]
Total bilirubin (μmol/L)	10.02 [6.93, 12.97]
Direct bilirubin (μmol/L)	3.25 [2.42, 4.18]
Alkaline phosphatase (U/L)	74.50 [57.25, 93.50]
Fasting blood glucose (mmol/L)	4.70 [4.40, 5.10]
Proteinuria *n* (%)	
Positive	3 (6)
Hematuria *n* (%)	
Positive	5 (10)
Audiometry *n* (%)	
>25 dB	0 (0)
Triiodothyronine (T3)	1.29 [1.12, 1.58]
Thyroxine (T4)	105.92 ± 16.59
Thyroid-stimulating hormone (TSH)	1.44 [0.80, 1.78]
Lens opacity *n* (%)	
Abnormal	2(4)
Dermatological assessments *n* (%)	
Abnormal	0 (0)
Micronucleus rate *n* (%)	
2‰	1 (2)
Chromosomal aberrations rate *n* (%)	
1%	1 (2)

IQR, interquartile range; SD, standard deviation.

According to the national standard GBZ 128–2019 (42), the target population includes medical radiation workers, industrial radiation workers, and others, excluding veterinary medicine. The distribution of workers across these three occupational categories in 2016–2020 is presented in Figure 1.

**Figure 1 fig1:**
[figure not shown]
Distribution of Chongqing radiation workers according to occupation from 2016 to 2020.

Although the number of industrial applications was small, the average annual individual effective dose was the highest (0.74 mSv). The average annual effective dose for radiation workers was 0.56 mSv in the past 5 years (6), below the worldwide average annual effective dose of 2.4 mSv from natural radiation sources, and far below the Chinese national standard personal dose limit of 20 mSv/ year (56, 57). The annual number of workers and their average annual effective dose are presented in Figure 2. Radiation workers in Chongqing have been exposed to low-dose ionizing radiation, with exposure levels exhibiting an overall downward trend over the past 5 years.

**Figure 2 fig2:**
[figure not shown]
The annual number of radiation workers and their average annual effective dose in Chongqing from 2016 to 2020.

Detailed information will be collected from Chongqing CDC personal dose monitoring system, including workers’ age, sex, marital status, education level, previous medical history, smoking, drinking, contact history of toxic and hazardous substances, occupational category, radiation working years (40, 58). The study design is presented in Figure 3.

**Figure 3 fig3:**
[figure not shown]
Flow chart of study design.

## Health outcomes

3

Radiation workers undergo routine health examinations at the Chongqing CDC, health examination outcomes will be collected from the National Radiation Health Information Platform (35). These evaluations encompass a comprehensive set of assessments, including complete blood count, biochemical blood analysis, urinalysis, audiometry, thyroid function tests, ophthalmic examinations, dermatological assessments, micronucleus analysis, and chromosome aberration analysis, among them, the complete blood count is the primary health outcome. All examinations were conducted by the Health Examinations Department. The outcomes of these health evaluations are monitored to identify potential radiation-related health risks.

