### Sample size calculation

2.3

Radiation exposure damages hematopoietic tissues, which is characteristic of occupational exposure. It has been proven that the hematological system, including mature functional cells, is susceptible to ionizing radiation (36). Ionizing radiation can cause early damage to the hematological system, therefore, blood cell counts are commonly used to assess its effects, a method widely used in the field (36).

The complete blood count served as the basis for sample size calculation. A sample size of 825 is considered sufficient to allow studies of the impact of radiation on human health. For example, according to references, the white blood cell count is commonly used to assess the effects of radiation on the health of a population (3, 4). The average white blood cell count for the population in the Chinese radiation group is (6.34 ± 1.40)*10 (9)/L, and in the normal population group is (6.59 ± 1.39)*10^9^/L.^5^ For a type I error of 0.05, a type II error of 0.1, and a power of 0.9, the sample size required is 660. Considering a 20% loss in follow-up (37, 38), the sample size increases to 825. Therefore, a recruitment sample of 825 radiation-exposed individuals will have sufficient power for the study. The sample size was estimated using G*Power software version 3.1 (Heinrich-Heine-Universität Düsseldorf, Düsseldorf, Germany) (39).

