#### Complete blood count

3.1.1

After fasting for at least 8 h, blood samples were collected into EDTA anticoagulant tubes, and blood collection time and volume should be recorded. Then, hematological parameters were analyzed by an automated blood cell analyzer (SYSMEX, XS-1000, Japan) (36).

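### The primary outcome is the whole complete blood count with no index named, under one blanket p<0.05, while the stated power relates to white cells only

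*Protocol article*

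**What the plan says.** - **Section 3, Health outcomes**, lists the routine examinations and says of them: "among them, the complete blood count is the primary health outcome".
- **Section 3.1.1, Complete blood count**, is the only entry under primary outcomes. It describes the measurement in the plural ("hematological parameters were analyzed by an automated blood cell analyzer") and neither lists nor ranks the indices.
- **Section 2.6, Table 1**, reports six blood-count indices for 50 workers in 2016: white cells, red cells, hemoglobin, platelets, hematocrit and mean corpuscular hemoglobin.
- **Section 2.3, Sample size calculation**, opens its calculation with "The complete blood count served as the basis for sample size calculation". It then works only with white cells, introduced as an example: "the white blood cell count is commonly used to assess the effects of radiation on the health of a population". The inputs are a mean of 6.34 (SD 1.40) in radiation workers and 6.59 (SD 1.39) in the normal population, type I error 0.05 and power 0.9. The results are 660, and 825 after 20% loss.
- **Section 2.5, Statistical analysis**, plans distributed lag non-linear models of dose and lag. Its only decision threshold is that p "values <0.05 were considered as statistically significant".

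**The concern.** A complete blood count is a set of measurements. Naming the set as the primary outcome leaves open which result answers the primary question. Under the text as written, several indices have equal primary standing and the only threshold is 0.05. Two consequences follow.

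1. **Type I error.** If several primary indices are each judged at 0.05, the chance that at least one is falsely positive exceeds 5%.
2. **Power.** Section 2.3 presents the panel as the basis of the sample size and concludes that the recruited number gives sufficient power for the study. The calculation supports that for one index, not for the primary outcome as section 3 defines it.

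These are separate effects. Sizing the study on white cells does not itself raise the false-positive rate. It shows that the outcome that was sized and the outcome declared primary are not the same.

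**Working it through.** **Step 1. Reproduce the plan's figure.**
Inputs from section 2.3: difference 6.59 − 6.34 = 0.25; SDs 1.40 and 1.39; alpha 0.05; power 0.90. Sidedness and allocation are not stated; two-sided and 1:1 are assumed.

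Pooled SD = √[(1.40² + 1.39²)/2] = 1.395.

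n per group = 2 × (1.960 + 1.282)² × 1.395² / 0.25² = 654.3, so 655 (656 with the t distribution).

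With the larger SD of 1.40 in place of the pooled value, the same formula gives 659.03, so 660 exactly. Other readings do not give 660: one-sided testing gives 534 per group, and a one-sample comparison with the pooled SD gives 328. The stated 660 is therefore a per-group number for a two-group comparison of mean white cell count.

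Loss to follow-up: 660 / (1 − 0.20) = 825, as stated.

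**Step 2. False-positive chance over the panel.**
Assumptions: the six Table 1 indices are the primary set, each has one test at two-sided 0.05, and there is no true effect on any of them.

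If independent: 1 − (1 − 0.05)⁶ = 1 − 0.95⁶ = 0.265.

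Blood-count indices are correlated, which lowers this. The article gives no correlations, so a range is shown, from simulation of six multivariate normal test statistics (400,000 draws each):

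| Common correlation | Chance of at least one p<0.05 |
|---|---|
| 0 (exact) | 26.5% |
| 0.3 | 24% |
| 0.5 | 21% |
| 0.7 | 16% |
| 0.9 | 11% |

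An assumed structure in which red cells, hemoglobin and hematocrit are strongly correlated (0.85 to 0.95) and the other pairs weakly or not at all gives about 21%.

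The result depends on how many indices count as primary. Under independence, 1 − 0.95ᵏ gives 9.8% for two, 14.3% for three, 22.6% for five and 40.1% for ten.

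**Step 3. Power if all six stay primary.**
This keeps the article's two-group framing, with 660 per group and pooled SD 1.395.

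Standardized difference = 0.25 / (1.395 × √(2/660)) = 3.256.

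- At alpha 0.05: Φ(3.256 − 1.960) = 0.90.
- With Bonferroni, alpha = 0.05/6 = 0.00833 and critical value 2.638: Φ(3.256 − 2.638) = 0.73.

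To restore 0.90 for white cells: 2 × (2.638 + 1.282)² × 1.395² / 0.25² = 956.8, so 957 per group, and 957 / 0.80 = 1,196.25, so 1,197 after 20% loss.

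With white cells as the single primary outcome, alpha stays at 0.05 and the stated 660 and 825 do not change.

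**The case against.** The strongest reply is that this is a condensed article on an observational cohort whose aim is to estimate exposure-lag-response associations. It sets no success criterion, and multiplicity methods, the form of the overall test and the reading of single lags are commonly left to an analysis plan that is not shown. This stands for those details, and their absence is not the point here. It does not cover the choice of primary variable. The article made that choice itself by naming a panel, and then sized the study on one member of it.

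It is also fair that Table 1 is not declared to be the list of primary indices, and that the 0.05 sentence does not describe testing index by index. Both are therefore marked as assumptions. Using one representative index for sizing is not in itself an error either.

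A reader might infer three stronger things that the article does not support:

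- **That a false primary positive is likely.** For six indices the chance stays at about 27% or below. Under independence it passes one half only at about 14 indices, a number the article does not give.
- **That any index at any lag would count as a primary success.** No such rule is stated. Testing several lags or doses separately would raise the error, but the article fixes no number of such tests.
- **That the conflicting earlier results described in the Discussion come from unordered panels.** The Discussion attributes the inconsistency to short follow-up, small cohorts and little attention to lag. Only the platelet findings clearly conflict.

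**Conclusion.** The point holds as a defect in how the primary outcome is fixed. Section 3 names a panel, section 2.3 sizes one index of it, and section 2.5 offers one unadjusted threshold. If the six Table 1 indices are each tested once at 0.05, the chance of at least one false primary positive is about 11% to 27%, roughly two to five times the nominal 5%. The upper end is independence and the lower end is a common correlation of 0.9. The stated 90% power applies to white cells alone; under Bonferroni over six indices it is about 0.73 at 660 per group.

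The power figures keep the article's own comparison of two group means. They say nothing about the power of a dose-lag cross-basis test among exposed workers, for which the article gives no calculation.

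**What to change.** **Preferred.** In section 3, name white blood cell count, the index used for the sample size, as the single primary outcome. In section 2.5, state one overall test of its dose-lag association at two-sided 0.05. List the other blood-count indices as secondary.

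**Alternative.** If the investigators want several primary indices, list them, state the multiplicity rule and restate the power: about 0.73 for white cells with Bonferroni over six at 660 per group, or 957 per group (1,197 after loss) to keep 0.90.

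**Cost.** The preferred option needs changes of wording in sections 2.5 and 3 and leaves 660 and 825 as they are. The other indices lose primary status, and which index best carries the primary question remains a scientific choice for the investigators. In either case section 2.3 should say that 660/825 comes from a two-group comparison of means and should not present it as the power of the cross-basis test. A power statement for that test would be additional work.
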